### **Concomitant or previous medical therapies**

9. has received any live virus or bacterial vaccinations within 12 weeks prior to first study treatment or is expected to receive any live virus or bacterial vaccinations during the study or up to 20 weeks after last study treatment.
10. has received B cell depleting therapy within 12 months prior to first administration of the study agent (e.g. rituximab, ocrelizumab or obinutuzumab).
11. has received a therapy that inhibits B-cell activating factor (BAFF) (i.e. belimumab) within 3 months prior to first administration of the study agent.

12. has received prior experimental immunosuppressive biologic therapy for lupus (other than that described as allowed), less than 5 half-lives or 6 months, whichever is longer prior to first administration of the study agent.
13. has used oral or IV cyclophosphamide within 2 months prior to first administration of the study agent.
14. has ever been exposed to daratumumab or any anti-CD38 antibodies (e.g. TAK-079, MOR202, isatuximab).

#### **Infection or predisposition to infection**

15. has a history of, or ongoing, chronic or recurrent infection, including but not limited to, chronic renal infection, chronic chest infection (e.g. bronchiectasis), sinusitis, recurrent urinary tract infection (e.g. recurrent pyelonephritis), an open, draining, or infected skin wound, or an ulcer.
16. Evidence of latent tuberculosis (as documented by a positive QuantiFERON-TB test at screening, no findings on medical history or clinical examination consistent with active tuberculosis, and a normal chest radiograph) except for participants that are willing to complete at least 4 weeks of anti-tuberculosis therapy as per WHO or national guidelines prior to randomization and agree to complete the remainder of treatment while in the study.
17. has or has had a serious infection (e.g. sepsis, pneumonia or pyelonephritis) or has been hospitalized or received IV antibiotics for a serious infection during the 3 months prior to consent.
18. Ongoing infection (requiring antibiotic treatment or fever > 38°C), including known HIV, active or chronic hepatitis B or hepatitis C.
19. has experienced a recent single dermatomal herpes zoster eruption within the past 6 months, or has a history of disseminated forms of zoster within the past 2 years prior to Screening.
20. has a history of hepatitis B surface antigen (HBsAg) or hepatitis C antibody (anti-HCV) positive, or other clinically active liver disease, or tests positive for HbsAg or anti-HCV at Screening.
21. has a history of human immunodeficiency virus (HIV) antibody positive, or tests positive for HIV at Screening.
22. have had an opportunistic infection (e.g. pneumocystis, aspergillosis, mycobacterium avium complex).
23. has a SARS-CoV-2 Infection at screening or baseline, confirmed by a PCR test (a rapid test is mandatory before each visit; if this test is positive, then a PCR test must be performed).

#### **Malignancy or increased potential for malignancy**

24. has a history of malignancy within 5 years before consent (squamous and basal cell carcinomas of the skin and carcinoma in situ of the cervix, or a malignancy which is considered cured with minimal risk of recurrence).
25. has a known history of lymphoproliferative disease, including lymphoma, or signs and symptoms suggestive of possible lymphoproliferative disease, such as lymphadenopathy of unusual size or location, or history of monoclonal gammopathy of undetermined significance.

### General exclusion criteria

26. pregnant, or breast-feeding, or planning to become pregnant while enrolled in this study or within 20 weeks after the last dose of study intervention or plans to father a child while enrolled in this study or within 20 weeks after the last dose of study intervention.
27. unable or unwilling to undergo multiple venipunctures because of poor tolerability or lack of easy access to veins.
28. is placed in an institution by court order or by order of the authorities.
29. is dependent on the investigator, sponsor or trial site (for example, as an employee)

## 5.3 ELIGIBILITY CRITERIA FOR LONG-TERM EXTENSION OBSERVATIONAL PERIOD

1. Participation in the DARALUP core-study
2. Written consent to the long-term extension of the observational period
3. If the patient is of childbearing potential, she agrees to: comply with effective contraceptive measures, has been using adequate contraception since the last menses, will use adequate contraception

## 5.4 PROHIBITIONS AND RESTRICTIONS

Potential subjects must be willing and able to adhere to the following prohibitions and restrictions to be eligible for participation:

- refer to Section 6.6 PROHIBITED THERAPY for additional details regarding therapies that are prohibited and restricted during the study.
- agree to follow all requirements that must be followed during the study as described in the Inclusion and Exclusion Criteria, Sections 5.1. and 5.2 (e.g. contraceptive requirements).
- agree to avoid excess exposure to natural or artificial (e.g. tanning beds, phototherapy) sunlight. In addition, it is advised that subjects maintain their typical use of sun protective measures (such as a hat, sunglasses, protective clothing, sunscreen). The time period for this requirement is from the start of screening until the last dose of study agent has been received.
- use of additional immunosuppressants or immunomodulators, other than those explicitly allowed in the inclusion/exclusion criteria (Section 5.1 and 5.2), are prohibited including but not limited to those listed in Section 6.9.
- must agree not to receive a live virus or live bacterial vaccination during the study.
- subjects must also agree not to receive BCG vaccination for 12 months after last dose of study agent, or any other live vaccine for 16 weeks after receiving the last administration of study agent.
- must agree not to receive an investigational medical device or an investigational drug other than study agent for the duration of this study.
- Skin concealers or topical tan preparations or nonpermanent tattoos should be avoided.
- within 48 hours before a study visit due to their potential to obscure skin disease activity.
- subjects should avoid use of any wigs or hair attachments that cannot be readily removed for scalp examination.
- Women of child bearing potential (WOCBP) must use a sufficient contraception during the time of study treatment, and 20 weeks thereafter. If the subject withdraws from the study prematurely, the 20 weeks must also be guaranteed.

Highly effective methods of contraception include:

- combined (estrogen and progestogen containing) hormonal contraception associated with inhibition of ovulation:
  - oral
  - intravaginal
  - transdermal
- progestogen-only hormonal contraception associated with inhibition of ovulation:
  - oral
  - injectable
  - implantable
- intrauterine device (IUD)
- intrauterine hormone-releasing system (IUS)
- bilateral tubal occlusion
- vasectomized partner
- sexual abstinence

In contrast to WOCBP, a postmenopausal status is defined as no menses for 12 months without an alternative medical cause. A high follicle stimulating hormone (FSH) level in the postmenopausal range may be used to confirm a post-menopausal state in women not using hormonal contraception or hormonal replacement therapy. However, in the absence of 12 months of amenorrhea, a single FSH measurement is insufficient to define a postmenopausal status.

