13. all women of childbearing potential (WOCBP) must have a negative highly sensitive serum (beta-human chorionic gonadotropin [betahCG]) test at screening and a negative urine pregnancy test prior to first dose of study agent. Also, they must use a sufficient method of contraception (see section 5.3 PROHIBITIONS AND RESTRICTIONS).
14. a male participant must wear a condom with spermicidal foam/gel/film/cream/suppository when engaging in any activity that allows for passage of ejaculate to another person and must agree not to donate sperm for the purpose of reproduction during the study and for a minimum of 20 weeks after receiving the last dose of study intervention.
15. willing and able to adhere to the lifestyle restrictions specified in this protocol.

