### 8.2 DISCONTINUATION OF STUDY TREATMENT

A participant will not be withdrawn from the study if he or she has to discontinue study agent before the end of the treatment regimen.

A subject's study agent must be discontinued if:

- Inclusion or exclusion criteria violation was noted after the subject started study drug, when continuation of the study drug would place the subject at risk as determined by the Investigator
- the Investigator, sponsor, and/or medical monitor believes that for safety reasons or tolerability reasons (e.g. adverse event), or due to severe, unstable, or rapidly progressive SLE disease activity, it is in the best interest of the subject to discontinue study agent.
- The subject (or the subject's legally acceptable representative) withdraws consent for administration of study drug.
- the subject develops study agent hypersensitivity (e.g. anaphylaxis, angioedema) reaction that is reported as serious or severe.
- the participant develops a serious opportunistic infection or SARS-CoV-2 infection confirmed by positive PCR-test (the follow-up phase can be continued once quarantine/COVID-symptoms/SARS-CoV-2 PCR positivity have resolved).
- if a new immunomodulator that is permitted per-protocol is initiated, then a participant will be considered a treatment failure but will not need to be withdrawn from the study.
- Occurrence of serious adverse events which are not compatible with the further administration of the study drug.

It is recommended that follow-up visit should be continued although patients might have discontinued study drug or had temporarily halt of study drug.

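### Section 5.4 bars live vaccines other than BCG for 16 weeks after the last dose, exclusion criterion 9 uses 20 weeks, and early leavers fall up to 28 days short

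*Protocol*

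**What the plan says.** Three statements in the protocol govern live vaccines from the first dose onward.

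- Exclusion criterion 9 in section 5.2 rules out anyone who "is expected to receive any live virus or bacterial vaccinations during the study or up to 20 weeks after last study treatment". The synopsis repeats it under the main exclusion criteria.
- Section 5.4 says a participant "must agree not to receive a live virus or live bacterial vaccination during the study".
- Section 5.4 then sets the limits after the last dose. For BCG, "subjects must also agree not to receive BCG vaccination for 12 months after last dose of study agent". For the rest, the undertaking is not to receive BCG in that time "or any other live vaccine for 16 weeks after receiving the last administration of study agent".

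The other safeguards that run on after dosing use 20 weeks. Male participants must not donate sperm "for a minimum of 20 weeks after receiving the last dose of study intervention" (section 5.1, criterion 14). Criterion 26 in section 5.2 excludes anyone "planning to become pregnant while enrolled in this study or within 20 weeks after the last dose of study intervention". The contraception bullet in section 5.4 also sets 20 weeks and adds: "If the subject withdraws from the study prematurely, the 20 weeks must also be guaranteed".

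On stopping the drug, section 8.2 says: "A participant will not be withdrawn from the study if he or she has to discontinue study agent".

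**The concern.** The drug, the vaccines (apart from BCG) and the starting point are the same in criterion 9 and section 5.4, but the durations differ by four weeks and no reason is given. Criterion 9 is judged once, at entry. Section 5.4 contains what the participant actually undertakes to do, and its 16-week statement is the only one about live vaccines other than BCG that continues after someone has left the study. Staff advising a departing participant would find two different answers.

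The subject is not trivial for this drug. It is given to deplete plasma cells, and section 2.1.4.5 reports a fall of roughly 60% in vaccine-induced antibodies in the two patients treated earlier. A live vaccine given too soon is the risk that both rules are meant to prevent. Early departure is also foreseeable: section 8.3 lists several events that end participation automatically, and section 9.2 plans for a 50% drop-out rate.

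**Working it through.** This is calendar arithmetic; no power or error-rate figure is involved.

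**Inputs**

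- Last dose after a full course: Day 49 (schedule of the core study period).
- Limit in section 5.4 for live vaccines other than BCG: 16 weeks = 16 × 7 = 112 days.
- Window in criterion 9: 20 weeks = 20 × 7 = 140 days.
- End of the core study: Day 241, window ±7 days (schedule). Dosing visits have a window of ±1 day.
- Final visit after withdrawal: 8 weeks = 56 days after the last dose (section 8.3).

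**The two limits after a full course**

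- Section 5.4: 49 + 112 = Day 161, the Week 24 visit day.
- Criterion 9: 49 + 140 = Day 189, the Week 28 visit day.
- Difference: 189 − 161 = 28 days.

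**Who is exposed**

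While on study, a participant is bound by the in-study ban. After leaving, only the 16-week undertaking remains. Someone who leaves *t* days after the last dose is therefore bound until max(*t*, 112) days after it, and the shortfall against criterion 9 is

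shortfall = max(0, 140 − max(*t*, 112)).

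| Days from last dose to withdrawal | Study day after a full course | Shortfall (days) |
|---|---|---|
| 112 or fewer | 161 or earlier | 28 |
| 119 | 168 | 21 |
| 126 | 175 | 14 |
| 133 | 182 | 7 |
| 140 or more | 189 or later | 0 |

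If only the first dose was given (Day 0), the limits are Day 112 and Day 140, and the maximum shortfall is again 28 days.

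**Completers**

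From last dose to the end of the core study is 241 − 49 = 192 days, which is 52 days beyond the 140 required. With the visit windows at their least favourable, it is (241 − 7) − (49 + 1) = 184 days, still 44 days beyond. The in-study ban therefore outlasts both limits for completers. It does so too for participants who stop the drug but stay in follow-up, because stopping does not withdraw them.

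**Does the withdrawal procedure close the gap?**

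No. After a full course the final visit falls on Day 49 + 56 = Day 105, before either limit.

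**Effect of the correction**

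Replacing 112 by 140 in the formula gives max(0, 140 − max(*t*, 140)) = 0 for every withdrawal time.

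**The case against.** Five arguments can be made for the text as it stands.

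1. *Section 5.4 imports the eligibility rules.* One of its bullets asks participants to keep to the requirements in sections 5.1 and 5.2 and gives contraception, which runs past the last dose, as the example. That makes the point arguable. However, the bullet is limited to requirements that apply while the study is running, so it does not reach someone who has left. It also leaves a different, explicit number for the same vaccines in the same list.

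2. *Both rules are entry conditions, and both can be met.* This is correct. Anyone expected at screening to receive a live vaccine within 20 weeks of treatment is already excluded. The exposed case needs three things together: departure before 20 weeks, a live vaccine not foreseen at entry, and its administration between the end of the participant's undertaking and week 20. This narrows the problem but does not remove it.

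3. *The 16-week rule runs from the last dose, so it already holds after withdrawal.* This stands as a reading. The sentence about premature withdrawal is therefore mainly a clarification, useful because the neighbouring contraception bullet has one and this bullet does not. It does not change the length of the undertaking, which is the actual conflict.

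4. *The other 20-week limits are reproductive safeguards.* This is also fair. On vaccines, the 20 weeks is one rule stated twice. The reproductive limits show the protocol's usual interval but cannot settle which vaccine interval was intended.

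5. *Nothing shows that 16 weeks is the wrong number.* The protocol justifies neither interval, and the antibody data come from two patients given four intravenous infusions, which cannot separate 16 from 20 weeks. Choosing 20 is the cautious resolution of a contradiction, not a derived value.

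**Conclusion.** The inconsistency is real and is in the current text. Section 5.4 does not permit a live vaccine at week 16, but the undertaking stops there, four weeks before the horizon used in criterion 9. For a participant who has left the study the shortfall is up to 28 days, falling to zero for departure 20 weeks or more after the last dose.

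This rests on reading the in-study ban as ending at withdrawal and on using the schedule's day numbers as printed. The number of participants affected cannot be estimated: the 50% drop-out figure is described as a conservative planning assumption, and the protocol gives no distribution of departure times and no likelihood of an unforeseen live vaccine.

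The severity is minor. Completers, the primary endpoint at Week 12 and the sample size are untouched.

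**What to change.** In section 5.4, change the limit for live vaccines other than BCG from 16 to 20 weeks after the last dose. Add a clause that the limit also applies after premature withdrawal, in line with the contraception bullet. Keep the 12-month BCG rule. Criterion 9 and the synopsis need no change.

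The cost is one number and one clause. The only disadvantage to a participant is that an early leaver may wait up to four weeks longer for a live vaccine.

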## 6 TREATMENT

### 6.1 TREATMENT ALLOCATION AND BLINDING

Not applicable because treatment assignment and blinding is not planned in this study (open-label study).

### 6.2 DOSAGE AND ADMINISTRATION

#### 6.2.1 STUDY DRUG ADMINISTRATION

Patients will receive 1800mg daratumumab as subcutaneous injection (Dara-SC) weekly for a total of 8 injections. This corresponds to two cycles of 4 Dara-SC weekly. Tight visit windows ( $\pm 1$  day) are required for study drug administration. Every effort should be made to keep subjects on the planned dosing schedule. Refer to Section 6.2.4 (DOSE DELAY AND MODIFICATION) for information on the management of delays in study drug administration.

Dara-SC will be provided as a fixed-dosed, combination drug product containing rHuPH20 drug substance (2000 U/mL) and daratumumab drug substance (120 mg/mL) in a single vial. Doses will be administered by manual push over approximately 3-5 minutes in the abdominal SC tissue in left/right locations, alternating between individual doses. The volume of the SC solution will be 15 mL for the 1800 mg dose. Refer to the Investigator's Brochure for additional guidance on SC administration of Dara-SC. Subjects need to be observed for 6 hours after the end of first daratumumab dose and if deemed necessary by the investigator after consecutive injections. All doses will be administered at outpatient visits. Subjects will receive predose medications and postdose medications as detailed in Sections 6.2.2 and 6.2.3.

#### 6.2.2 PREDOSE MEDICATION

All subjects will receive a premedication to prevent IRR approximately 1 to 3 hours prior to each study drug administration (1 hour prior to study drug administration is preferred) with:

- An antipyretic: paracetamol (acetaminophen) 650-1000mg orally and
- An antihistamine: diphenhydramine 25-50mg or equivalent, orally or i.v. and
- A corticosteroid: dexamethasone 20mg or equivalent for the first 2 doses and 10mg for all subsequent doses (in the absence of IRR adverse event in the first two doses), orally or i.v.

No additional corticosteroids (e.g. prednisolone) should be used as a background regimen on daratumumab application days when patients have received dexamethasone as premedication prior to injection.

#### 6.2.3 POSTDOSE MEDICATION

To reduce the risk of prolonged injection related reactions (IRR), 20mg methylprednisolone (or equivalent) will be administered orally on the first two days post daratumumab injection, unless patients are on chronic background glucocorticoid therapy with daily prednisolone equivalent of at least 5mg daily. If after the first three daratumumab injections no IRR occur, administration of glucocorticoids will not be necessary, also in those participants who have no or less than 5mg daily prednisolone (or equivalent) background therapy.

#### 6.2.4 DOSE MODIFICATION AND DELAYS

Dose modification of 1800 mg Dara-SC (increase or decrease) is not permitted. In total, 8 Dara-SC injections are planned, particularly 2 cycles of 4 injections administered weekly. Changes of dosing interval should not affect the following study drug administration, unless the previous dose was administered within the previous 3 days, because a minimum of 4 days between daratumumab doses is required. If doses of the study drug are skipped, they will not be additionally included in the treatment schedule. An extension of treatment period is not allowed. Subjects will continue to receive study treatment until Week 8, unless occurrence of unacceptable toxicity, or other reasons as listed in Section 8.2 DISCONTINUATION OF STUDY TREATMENT.

Dose delay resembles a method for managing potential occurring daratumumab-related toxicities. Before each dose of study drug, the subject will be evaluated by the treating physician for possible toxicities that may have occurred after the previous dose(s). Delay in study drug administration will be based on the toxicity experienced during the previous injections. Toxicities are to be assessed according to NCI-CTCAE, Version 5.0 (see also section 10.3 SEVERITY CRITERIA).

The study treatment must be held if any of the following criteria are met, to allow for recovery from toxicity, regardless of relationship to study drug:

- Grade 3 or higher hematologic toxicity
- Grade 3 or higher non-hematologic toxicities
- Febrile neutropenia
- Hypogammaglobulinemia requiring IVIG substitution according to criteria provided in section 6.4.3 IMMUNOGLOBULINE SUBSTITUTION

Study treatment should be resumed when the toxicity has resolved to  $\leq$  Grade 2 except for laryngeal edema, bronchospasm or febrile neutropenia, which must be fully recovered (see also section 7.6.2 INJECTION RELATED REACTIONS AND INJECTION SITE REACTIONS). Infusion-related reactions may occur upon re-initiation of daratumumab after a prolonged delay in treatment. Investigators should consider the applicable infusion reaction guidance provided in sections 6.2.2 (PREDOSE MEDICATION) and 6.2.3 (POSTDOSE MEDICATION). Subjects missing  $\geq 3$  consecutive planned doses of study drug for reasons other than toxicity should be withdrawn from treatment, unless, upon consultation with the sponsor and the review of safety and efficacy, continuation is agreed upon.

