| Dosage and administration of the study drug:                           | 
Patients will receive 1800mg daratumumab as subcutaneous injection (Dara-SC) weekly for a total of 8 injections. This corresponds to two cycles of 4 Dara-SC weekly. Tight visit windows (<math>\pm 1</math> day) are required for study drug administration and every effort should be made to keep subjects on the planned dosing schedule. Nevertheless, dose modifications may be required in case of adverse events. Doses will be administered by manual push over approximately 3-5 minutes in the abdominal SC tissue in left/right locations, alternating between individual doses. The volume of the SC solution will be 15 mL for the 1800 mg dose. All doses will be administered at outpatient visits. Subjects will receive predose medications and postdose medications.
                                                                                                                                                                                                                                                                                                                                                                                                                                                                                                                                                                                                                                                                                                                                                                                                                                                                             |

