### 7.6.2 INJECTION RELATED REACTION and INJECTION SITE REACTIONS

An injection related reaction (IRR) is defined as any adverse reaction that occurs during or short after an application of the study drug. Daratumumab injection solution for subcutaneous application can cause severe and/or serious IRRs, including anaphylactic reactions. Symptoms of IRRs can be respiratory symptoms like stuffy nose, cough, and irritation of throat, allergic rhinitis, wheezing respiration as well as pyrexia, chest pain, itching, chills, vomiting, nausea and hypotension. Severe IRRs that may occur include bronchospasm, hypoxia, dyspnea, hypertension and tachycardia (see also the Investigator's Brochure).

An injection site reaction (ISR) is any adverse event that occurs at or around the injection site and is time-related to the last administration of test drug. Patients should be monitored for the occurrence of injection site reactions and/or generalized allergic reaction. Therefore, subjects need to be observed for 6 hours after the end of first daratumumab dose and if deemed necessary by the investigator after consecutive injections. Permanent discontinuation of study agent must be considered for patients who experience an adverse event of injection reaction that is judged serious or severe by the Investigator, e.g. allergic reaction, anaphylaxis (see also section 8.2 DISCONTINUATION OF STUDY TREATMENT). If the subject experiences a Grade 2 or higher event of laryngeal edema, or a Grade 2 or higher event of

bronchospasm that does not respond to systemic therapy and does not resolve within 6 hours from onset, then the subject must be withdrawn from daratumumab treatment.

Administration of daratumumab may be restarted upon recovery from toxicity to Grade  $\leq 2$  or baseline, apart from laryngeal edema, bronchospasm or febrile neutropenia, which must be fully recovered (see also section 6.2.4 DOSE MODIFICATION AND DELAYS). If a laryngeal edema or bronchospasm occurs, the Sponsor-Investigator must be contacted prior to any further application of daratumumab to discuss and assess the risks and benefits of further exposure to daratumumab in the trial.

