### 10.3 SEVERITY CRITERIA

An assessment of severity grade of each AE will be made according to NCI-CTCAE, Version 5.0. In general, toxicity is graded as mild (Grade 1), moderate (Grade 2), severe (Grade 3), or life-threatening (Grade 4), with specific parameters according to the organ system involved. Death (Grade 5) is used for some of the criteria to denote a fatality occurring during treatment.

The Investigator should use clinical judgment in assessing the severity of events not directly experienced by the subject (e.g. laboratory abnormalities, physical examination).

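### For severe allergic injection reactions, section 7.6.2 makes stopping discretionary and section 8.2 makes it mandatory; the laryngeal edema rules also conflict, and the passages must be reconciled.

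*Protocol*

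**What the plan says.** Four places in the protocol govern dosing after an injection reaction.

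- **Section 6.2.4** requires treatment to be held for any non-hematologic toxicity of Grade 3 or higher, whatever its cause. It then states: "Study treatment should be resumed when the toxicity has resolved to" Grade 2 or lower. The exceptions are laryngeal edema, bronchospasm and febrile neutropenia, which must recover fully first. The sentence cross-refers to 7.6.2. Earlier in the same section, treatment runs to Week 8 unless there is unacceptable toxicity or a reason listed in 8.2.
- **Section 7.6.2** states: "Permanent discontinuation of study agent must be considered for patients who experience an adverse event of injection reaction that is judged serious or severe", with allergic reaction and anaphylaxis as examples and a pointer to 8.2. The next rule begins "If the subject experiences a Grade 2 or higher event of laryngeal edema" and continues with Grade 2 or higher bronchospasm that neither responds to systemic therapy nor resolves within 6 hours; such a subject must be withdrawn from daratumumab treatment. The following paragraph allows restart at Grade 2 or lower "or baseline, apart from laryngeal edema, bronchospasm or febrile neutropenia, which must be fully recovered". It requires contact with the Sponsor-Investigator before any further dose after laryngeal edema or bronchospasm.
- **Section 8.2** lists, among the reasons for which study agent must be discontinued: "the subject develops study agent hypersensitivity (e.g. anaphylaxis, angioedema) reaction that is reported as serious or severe".
- **Section 10.3** supplies the grading scale: "mild (Grade 1), moderate (Grade 2), severe (Grade 3").

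On dose changes, the synopsis says "Nevertheless, dose modifications may be required in case of adverse events", and 6.2.4 says "Dose modification of 1800 mg Dara-SC (increase or decrease) is not permitted".

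**The concern.** Sections 7.6.2 and 8.2 set the same threshold (serious or severe) and share an example (anaphylaxis), but one leaves the decision open and the other closes it. An investigator working from 7.6.2 could re-dose a patient whom 8.2 requires to be stopped. Laryngeal edema raises the same problem between 7.6.2 and 6.2.4, and within 7.6.2 itself.

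The first issue is patient safety, since re-exposure after a severe reaction should not depend on which section is consulted. The second is exposure. Under 6.2.4 skipped doses are not made up and the treatment period may not be extended, so the rule applied fixes how much drug the patient receives before the Week 12 primary endpoint. With 10 patients planned, one patient is 1/10 = 10% of the sample.

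**Working it through.** The protocol has no figure to reproduce here. The check is to put the same event through each section.

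**Case A: Grade 3 allergic injection reaction or anaphylaxis that improves to Grade 2 or lower.** Section 10.3 makes Grade 3 severe, so the thresholds in 7.6.2 and 8.2 are both met.

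| Section | Outcome |
|---|---|
| 6.2.4, resume sentence | Hold, then resume; the event is not among the exceptions |
| 6.2.4, earlier sentence | Treatment continues unless an 8.2 reason occurs |
| 7.6.2 | Stopping must be considered; restart may follow recovery |
| 8.2 | Must be discontinued |

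A rule that leaves the choice open and one that removes it cannot both govern the same event. The pointer from 7.6.2 to 8.2 does not say which prevails. The 6.2.4 leg can be reconciled with 8.2 through its earlier sentence, but that proviso is not attached to the resume sentence, which sends the reader to 7.6.2.

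**Case B: laryngeal edema.**

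| Grade | 6.2.4 | 7.6.2, withdrawal rule | 7.6.2, next paragraph |
|---|---|---|---|
| 2 | Below the Grade 3 hold criterion | Withdraw from treatment | Restart after full recovery, with prior sponsor contact |
| 3 or higher | Hold, resume after full recovery | Withdraw from treatment | Restart after full recovery, with prior sponsor contact |

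On the natural reading, every laryngeal edema held under the Grade 3 criterion of 6.2.4 is one that 7.6.2 withdraws. The laryngeal edema exception in 6.2.4 then has no case to act on under that criterion. The restart paragraph in 7.6.2 is not limited to lower grades.

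**Case C: bronchospasm.** The withdrawal rule covers Grade 2 or higher events that do not respond and do not resolve within 6 hours. Bronchospasm that resolves in time falls under the restart text without conflict. An event that outlasts 6 hours and later recovers fully meets the words of both rules, so how they fit together needs stating.

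**Doses received, for a Case A reaction at dose 1:**
- Stopped: 1 of 8.
- Resumed, recovered before the next weekly visit: 1 + 7 = 8 of 8 if no later dose is lost.
- Resumed after one skipped visit: 1 + 6 = 7 of 8, because skipped doses are not replaced.

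**Modified intention-to-treat set (9.3).** It excludes patients with a dose interruption for an adverse event and patients who discontinue study treatment.
- Reaction outlasts the next weekly dose: the interruption excludes the patient, and so would a permanent stop. Membership is the same.
- Reaction resolves before the next weekly dose: resuming leaves no interruption and the patient stays in; stopping excludes the patient. Membership differs.

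The main analysis in 9.3 includes all enrolled patients in either case.

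**The case against.** The strongest reply is that the protocol, read as a whole, already has a hierarchy. Section 6.2.4 is a general toxicity rule that gives way to 8.2, and 7.6.2 points to 8.2. This largely stands for 6.2.4, so a reader who infers three irreconcilable rules goes too far. It does not settle 7.6.2 against 8.2, because the pointer leads to a conflicting instruction without ranking it.

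Second, an injection reaction as defined in 7.6.2 is wider than hypersensitivity and includes fever or nausea. That is correct and limits the conflict to allergic reactions and anaphylaxis. Those are the examples 7.6.2 itself gives.

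Third, the condition of no response and no resolution within 6 hours could grammatically attach to laryngeal edema as well. That would narrow Case B, but the sentence gives laryngeal edema its own grade and separates it from bronchospasm, so the natural reading is the unconditional one. An ambiguity on this point is itself reason to rewrite the sentence.

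Other inferences should be resisted:

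- **A high chance that the conflict arises.** Section 2.1.4.2 reports reactions in 11 of 45 myeloma patients at 1800 mg (24.4%), which would give 1 − (34/45)^10 = 0.94 for at least one among 10. That counts reactions of any grade, generally Grade 1 or 2, which do not trigger Case A. No Grade 3 count is given.
- **A patient barred from restarting by a baseline abnormality.** Only 7.6.2 allows return to baseline as an alternative, but it does so in the injection-reaction section, and 6.2.4 assesses toxicities arising after earlier doses. Applying the difference to, say, a low lymphocyte count at entry is strained.
- **A permitted dose reduction.** The synopsis sentence follows one about keeping to the dosing schedule and can be read as meaning delays. No reduced dose is described.

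**Conclusion.** The point holds in a bounded form. The firm contradiction is between 7.6.2 and 8.2 for serious or severe allergic injection reactions and anaphylaxis. A second lies between the laryngeal edema withdrawal rule in 7.6.2 and the restart text in 6.2.4 and in 7.6.2's own next paragraph; it rests on the natural reading of the withdrawal sentence. The 6.2.4 resume sentence adds to the confusion but is softened by that section's deference to 8.2. Bronchospasm needs clarification rather than correction.

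For an affected patient, the section applied decides on re-exposure and, for a reaction at dose 1, between 1 of 8 doses and up to 8 of 8. A reader might infer that it always changes the modified intention-to-treat set; it does so only if the reaction resolves before the next weekly dose. Such cases may be few, and their frequency cannot be derived from the protocol. Because the text is wrong as written and bears on patient safety, it should be corrected regardless. The baseline wording and the synopsis wording are minor.

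**What to change.** The sponsor should reconcile 6.2.4, 7.6.2 and 8.2 into one hold, restart and stop rule set, for example a single table, and have each section refer to it. It should cover:

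- serious or severe hypersensitivity, including anaphylaxis;
- laryngeal edema, by grade;
- bronchospasm, by grade, stating how the 6-hour condition relates to restart after full recovery, and whether that condition applies to laryngeal edema;
- where the required contact with the Sponsor-Investigator applies, since 6.2.4 does not repeat it.

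Which rule applies in each case is the sponsor's clinical decision; this review takes no position on it. As minor edits, align the baseline alternative in 7.6.2 with the restart threshold in 6.2.4, and the synopsis phrase on dose modifications with 6.2.4.

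The cost is wording in one protocol amendment, with no new visits, procedures or patients.
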